### Analysis of immunogenicity

Two analyses will be performed: Total Cohort and ATP Cohort.

For each treatment group, the seropositivity rate for anti-CS antibodies (proportion of subjects with anti-CS antibody titres of  1 µg/ml) and its 95% CI will be tabulated by vaccine dose. Antibody titres will be summarized by geometric mean titres (GMTs) of CS repeat antibodies (anti R32LR) measured in µg/ml. 95% CI of GMTs will be calculated for all time points at which serology samples are taken. Reverse cumulative curves will be plotted for antibody titres measured at month8½. GMT calculations are performed by taking the anti-log of the mean of the log titre transformations ***(log base 10)***. Antibody titres of < 1µg/ml will be given an arbitrary value of 0.5 µg/ml for the purpose of GMT calculation.
**(Amended January 17, 2003)**

For each treatment group in Cohort 2, the seroprotection rate for anti-HBs antibodies (proportion of subjects with anti-HBs antibody titres of  10 mIU/ml) and its 95% CI will be tabulated by vaccine dose. GMTs for anti-HBs antibodies measured in mIU/ml with 95% CI will be calculated for each group at each time point when a serology sample is available. Reverse cumulative curves will be plotted for anti-HBs antibody titres measured at month 8½. GMTs for anti-RF1-like antibodies, measured in EL.U/ml, with 95% CI will be calculated for each group at each time point when serology sample is available. For GMT calculations, antibody titres below the cut-off of the assay (10 mIU/ml) will be given an arbitrary value of half the cut-off for the purpose of calculating the GMTs.

Number and percentage, with 95% CI, of children of 18 months of age or more at first vaccination with seroprotective levels of anti-HBs antibodies (seroprotective levels are defined as anti-HBs titres of 10 mIU/l or greater) at day 90 will be computed.

***This study will compare the immunogenicity of (Engerix-B™) and RTS,S/AS02A. A non-inferiority approach will be used to calculate the power of the study for the comparison of seroprotection rates and geometric mean titres of anti-HBs antibodies. From census information gathered by CISM, approximately 25% of the population will be less than 24 months of age. Therefore the assessment of the anti-HBs antibody immune response will be based on approximately 248 evaluable subjects (124 subjects per group). This sample size will have 89% power at a 2.5% significance level using a one-sided equivalence test of proportions when the proportion that are seroprotected in the control group (subjects vaccinated with Engerix-B™) is at least 0.95 and the proportion in the RTS,S/AS02A group (subjects of 24 months of age or more) is 0.95 and the maximum allowable difference between these proportions that still results in equivalence (the range of equivalence) is 0.10 (PASS 2000, one sided equivalence test of proportions, alpha = 2.5%).***~~The difference between seroprotection rates at month 4 for anti-HBs antibodies between both groups will be calculated as well as the 90% CI around these difference. If the lower limit of the two-sided 90% CI (corresponding to a one-sided 95% CI) is greater than –10%, non-inferiority of RTS,S/AS02A compared to Engerix-B™ will have been demonstrated in this study.~~

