**Final version of protocol: May 8, 2002 (Final version)**

**Amendment 1: August 13, 2002 (Final version)**

**Amendment 2:** **January 17, 2003 (****Final version)**

| **Coordinating Author: [name]**  **Rationale/background for changes:**   1. Change in age cut-off for control vaccine regimes   In agreement with the Principal Investigator, vaccines were selected for the control group that were of benefit to the study children (the rationale for the choice of control vaccines is explained in section 1.2.2.4).  Hepatitis B vaccination (at 2, 3 and 4 months of age in combination with diphtheria-tetanus-pertussis and polio vaccines) was introduced into the EPI schedule of Mozambique in July 2001. It is estimated that 83% of children have received all immunizations by 12 months of age (personal communication from [name]). Re-immunization with a hepatitis B vaccine would not provide any individual benefit to study children therefore two different vaccination regimes were planned. With a proposed study start in November 2002, it was previously envisaged that only children under the age of 18 months at first vaccination would have received immunisation against hepatitis B as part of their EPI. Therefore, the selected vaccination regimes for the control group were dependent on the age of the child at first vaccination:   - 3 doses of hepatitis B vaccine (Engerix‑B™) to children of 18 months and older. - 2 doses of a 7-valent pneumococcal conjugate vaccine (Prevnar®, Wyeth Lederle Vaccines) at first and third vaccination and 1 dose of Haemophilus influenzae type b vaccine (Hiberix™) at second vaccination to children less than 18 months.   There has been a delay to the start of the study. As a consequence, the proportion of children within the study population that have previously received hepatitis B vaccination will increase: it is now anticipated that children of up to 24 months of age approximately will have received hepatitis B vaccination as part of their EPI, by study start. To ensure that these children benefit from their control vaccine regime, the age range for the control vaccination regime of two doses of Prevnar® and one dose of Hiberix™ will be extended from children less than 18 months to children less than 24 months.  The following sections will be amended: Synopsis, 1.2.2.4, 3, 5.2.2, 5.2.12, 6.1.2, 6.1.3, 6.1.4, 6.4, 6.6, 10.6.2 and Appendix G.  The exclusion criterion for previous hepatitis B vaccination will now be amended to exclude children of 24 months of age and above that have previously received a hepatitis B vaccination (see section 4.4).  This amendment to the vaccination regimes will not affect the vaccination schedules for Prevnar® and Hiberix™. The vaccination schedules for both vaccines comply with the manufacturer’s instructions for children of 12 to 24 months (two doses of Prevnar® at least 2 months apart and one dose of Hiberix™). | | | | |

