### Hepatitis B vaccine (Engerix-B™)

Hepatitis B vaccine (Engerix-B™) is the control vaccine to be given to children of ***24*** ~~18~~ months old or more. The paediatric dosage vial contains 10 µg of purified major hepatitis B surface antigen. It is prepared as a suspension of 0.5 ml volume per vial. The content, upon storage may present a fine white deposit with a clear colourless supernatant. Once shaken the vaccine is slightly opaque.

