**(Amended January 17, 2003)**

GMTs for anti-HBs antibody titres at month 4 between both groups will be calculated as well as the 90% CI around the ratio of GMTs (RTS,S/AS02A / Engerix-B™). If the lower limit of the two-sided 90% CI (corresponding to a one-sided 95% CI) is greater than 0.5, then non-inferiority of RTS,S/AS02A compared to Engerix-B™ will have been demonstrated.

The assessment of non-inferiority for seroprotection rates and GMT ratios will be conducted on all subjects (regardless of whether subjects are seropositive or seronegative for HBsAg at baseline) and on HBsAg seronegative subjects only.

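### Section 10.7.4 still computes day-90 anti-HBs seroprotection from 18 months of age and in mIU/l, and it no longer states a seroprotection decision rule that would settle the population

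*Supplement*

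**What the plan says.** Section 10.7.4 asks for a count and a percentage, with a 95% confidence interval, of "children of 18 months of age or more at first vaccination with seroprotective levels of anti-HBs antibodies" at day 90. It defines seroprotection in that sentence as a titre of "10 mIU/l or greater". The sentence carries no amendment mark.

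Amendment 2 moved the age at which the control regimen changes. Its rationale says that the age range for Prevnar and Hiberix "will be extended from children less than 18 months to children less than 24 months". Sections 3, 5.2.2 and 6.1.2 accordingly give Engerix-B to controls of 24 months or more. The amendment's list of sections changed for the new age limit includes 10.6.2 but not 10.7.4.

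The paragraph after the 18-month sentence was rewritten. It says that "approximately 25% of the population will be less than 24 months of age", arrives at 124 evaluable children per group, and describes the RTS,S/AS02A group in its power statement as "subjects of 24 months of age or more) is 0.95". The former rule (difference in seroprotection rates, confidence interval, limit of -10%) is struck out and no new rule replaces it. The Amendment 2 rationale, however, says that the 90% interval was to become a 95% interval in this section. The section closes by saying that non-inferiority is assessed on all subjects, "regardless of whether subjects are seropositive or seronegative for HBsAg at baseline) and on HBsAg seronegative subjects only", with no age limit.

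**The concern.** Control children of 18-23 months receive no study dose of hepatitis B vaccine. A seroprotection rate for the control group that includes them is not a rate for Engerix-B recipients. RTS,S/AS02A recipients of the same age do receive a vaccine containing the hepatitis B surface antigen.

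The 18-month sentence is the only current sentence in 10.7.4 that states an age group for computing the day-90 rate. Someone programming from that section meets an 18-month rule, a power statement for 24 months or more, and a closing sentence that says all subjects. If the 18-month set were used for the test, a lower control rate would tend to help RTS,S/AS02A meet a 10-point margin. Section 5.2.12 makes the end-of-study plan for RTS,S/AS02A recipients depend on the result of that comparison.

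**Working it through.** **Inputs from the documents.** Cohort 2 enrolment 416; 20% lost or not evaluable; 1:1 allocation; 25% under 24 months; 12.5% under 18 months (the struck census figure in 10.6.2); seroprotection 0.95 in both groups; margin 0.10; one-sided alpha 2.5%; 83% of children with all EPI immunisations by 12 months (section 1.2.2.4).

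**1. The plan's own figures.** 416 × 0.80 × 0.75 = 249.6, in line with the stated 248 (124 per group). With 124 per group, 0.95 against 0.95 and margin 0.10, the Farrington-Manning score test gives 88.9% power, which reproduces the stated 89%. These figures therefore belong to children of 24 months or more.

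**2. The set selected by the 18-month sentence.** 416 × 0.80 × 0.875 = 291, about 145 per group. Of these controls, 145 - 124 = 21 are aged 18-23 months. As a share this is (25 - 12.5)/87.5 = 14.3%, or 1 in 7. The calculation assumes equal loss by age.

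**3. Effect if that set were carried into the test.** Put the true RTS,S/AS02A rate in children of 24 months or more on the margin: 0.85 against 0.95. Let q be the protected share among controls of 18-23 months, which the documents do not give.

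- Control rate: pC = (124/145) × 0.95 + (21/145) × q. The RTS,S/AS02A rate pT is mixed in the same way.
- SE = √{[pC(1 - pC) + pT(1 - pT)]/145}.
- Chance of declaring non-inferiority = Φ[(0.10 + pT - pC)/SE - 1.96].

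In the clean set of 124 per group the difference is -0.10 and the chance is Φ(-1.96) = 2.5%.

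| q, controls 18-23 months | RTS,S/AS02A, 18-23 months | pC | pT | Difference | Chance of declaring non-inferiority |
|---|---|---|---|---|---|
| 0.79 (0.83 × 0.95) | 0.85 | 0.927 | 0.850 | -0.077 | 9% |
| 0.79 | 0.95 | 0.927 | 0.864 | -0.062 | 18% |
| 0.95 | 0.85 | 0.950 | 0.850 | -0.100 | 2.5% |
| 0.95 | 0.95 | 0.950 | 0.864 | -0.086 | 6% |

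Simulation with Newcombe intervals gives 9% and 17.5% for the first two rows.

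**4. The unit.** 10 mIU/l is one thousandth of 10 mIU/ml. The preceding paragraphs of 10.7.4, sections 1.2.1.1 and 5.2.12, and the assay table in 5.8.3 all use 10 mIU/ml.

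**The case against.** The strongest reply is that the quoted sentence is not the non-inferiority test. It asks for a number, a percentage and an interval. It states no between-group difference and no margin, and it names no Engerix-B comparator. The test population is described elsewhere: the sample-size table in the Amendment 2 rationale counts children of 24 months or more receiving RTS,S/AS02A or Engerix-B, and section 10.6.2 and the footnote to Table 7 use the same cut-off. An 18-month set would give about 145 per group, not the 124 in the next paragraph. All of this stands.

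A reader might therefore go too far in inferring that the planned test compares RTS,S/AS02A with a diluted control group and so favours non-inferiority. The documents do not support that. The error rates above need both the 18-month set in the test and assumed protection rates in the younger children. Nor can those controls be treated as unprotected, since section 1.2.2.4 expects most children under 24 months to have had EPI hepatitis B vaccine.

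The unit slip should have no analytic effect, because 10 mIU/ml is defined just before it and is the assay cut-off. The reporting and analysis plan, not shown here, may also state the rule.

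The reply does not remove the conflict. The rationale for Amendment 2 points to 10.7.4 for the 95% interval rule, and 10.7.4 does not contain it. Margin and alpha can be inferred from the power statement, but the section leaves the population open to two readings.

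**Conclusion.** The point holds as an inconsistency in a stated analysis rule. Age limit and unit in the day-90 seroprotection sentence contradict the rest of the amended protocol. As written, about 14% of the controls in that rate (about 21 of 145) would have been assigned Prevnar and Hiberix. That figure rests on the struck 12.5% census share and equal loss by age.

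Any effect on the non-inferiority conclusion is conditional. If the 18-month set were used, the bias would tend to favour RTS,S/AS02A: a one-sided error of about 9-18% with 79% protection in controls of 18-23 months, and about 2.5-6% with 95%. The missing decision rule is what makes this more than a clerical slip. The objective is secondary and confined to Cohort 2.

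**What to change.** In section 10.7.4:

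- Change 18 to 24 months and mIU/l to mIU/ml.
- State that the seroprotection and GMT comparisons are restricted to Cohort 2 children of 24 months or more at dose 1 who received RTS,S/AS02A or Engerix-B, and make the closing sentence on all subjects refer to that set.
- Restore the seroprotection criterion in the form the Amendment 2 rationale intends: difference at day 90, lower limit of the two-sided 95% confidence interval above -10%. Name day 90 explicitly, because the struck rule referred to month 4, when no serology sample is scheduled.

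These changes are wording only and need no new data. Any analysis plan should carry the same text before unblinding.

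As a secondary suggestion, pre-specify an analysis in children with day-0 anti-HBs below 10 mIU/ml. The current baseline split uses HBsAg, so a child already protected on day 0 counts as seroprotected whichever vaccine was given. Anti-HBs is already measured on day 0 in Cohort 2. The cost is power: at one-sided 2.5%, about 85% with 112 per group and 80% with 99. Table 7 prints 92 and 89 for these sizes, which correspond to a one-sided 5% level.

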**(Amended January 17, 2003)**

GMTs for anti-HBs antibody titres at month 4 between both groups will be calculated as well as the 90% CI around the ratio of GMTs (RTS,S/AS02A / Engerix-B™). If the lower limit of the two-sided 90% CI (corresponding to a one-sided 95% CI) is greater than 0.5, then non-inferiority of RTS,S/AS02A compared to Engerix-B™ will have been demonstrated.

The assessment of non-inferiority for seroprotection rates and GMT ratios will be conducted on all subjects (regardless of whether subjects are seropositive or seronegative for HBsAg at baseline) and on HBsAg seronegative subjects only.

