### Cross-over immunisation at study end

***One of the aims of Cohort 2 is a formal comparison of the immune response to the HBsAg of RTS,S/AS02A to Engerix-B™ (see sections 10.6.2 and 10.7.4). If non-inferiority of the seroprotective anti-HBs response induced by RTS,S/AS02A, as compared to that afforded by Engerix-B™, is demonstrated in the statistical comparison, then no cross-over immunisation of the malaria vaccine group with the Engerix-B™ control vaccine is planned. However, if non-inferiority is not demonstrated, the following rescue plan for all recipients of RTS,S/AS02A will be initiated at study end (month 21) but will not be considered as a study procedure and therefore will not be documented in the CRF. All children of 24 months or more at first vaccination in the RTS,S/AS02A group will be offered, at study end, a blood test to determine their anti-HBs antibody titre. Those children with a titre below the protective titre of 10 mIU/mL will be offered by the investigator one or more doses of Engerix-B™ (commercial presentation) to assure seroprotective levels are attained.*** ~~as the RTS,S/AS02A malaria vaccine contains the same antigen that is in Engerix‑B™. However,~~ In addition, any subject of ***24*** ~~18~~ months or more at first vaccination that cannot be vaccinated within 7 days of the originally scheduled date for vaccination, will be offered at the end of the study additional doses of Engerix-B™ (commercial presentation) under the responsibility of the investigator.

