***Immunogenicity***

- Titres of anti-CS antibodies at the following time points for which serology samples are analyzed: days 0, 60 and 90, month 8½.
- Titres of anti-HBs antibodies at the following time points for which serology samples are analyzed: days 0 and 90, month 8½.

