***Immunogenicity***

- Titres of anti-HBs and anti-CS antibodies at the following time points for which serology samples are analyzed: month 21.

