**(Amended January 17, 2003)**

Similarly this sample size will provide 99% power to demonstrate at 10% significance level using an equivalence of means test, that the lower limit of a two sided 90% confidence interval on the GMT ratio of anti-HBs antibodies (RTS,S/AS02A vaccine group over Engerix-B™ vaccine group ) is greater than 0.5 (2 fold decrease). (PASS 2000, equivalence of means, alpha = 10%). The standard deviation used for this calculation was 0.591 ***(computed on log base 10 transformed tires)*** and was derived from a GSK Biologicals study (DTPw-HBV-033) in which three doses of vaccine were administered to each subject at 3 months, 4 months and 5 months of age[[35]](#endnote-36).

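### Section 10.7.4 sets the hepatitis B GMT comparison at month 4, when no serum is drawn, judges it at one-sided 5% against 2.5% for seroprotection, and gives seroprotection no explicit success criterion

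*Supplement*

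**What the plan says.** The current protocol is the version amended on January 17, 2003.

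- **GMT rule (10.7.4).** "GMTs for anti-HBs antibody titres at month 4 between both groups will be calculated as well as the 90% CI around the ratio of GMTs". The criterion follows: "If the lower limit of the two-sided 90% CI (corresponding to a one-sided 95% CI) is greater than 0.5", non-inferiority will have been shown. Section 10.6.2 powers the comparison the same way, on "the lower limit of a two sided 90% confidence interval on the GMT ratio of anti-HBs antibodies", and states 99% power.
- **Serum schedule.** Section 10.3.2 lists "Titres of anti-HBs antibodies at the following time points for which serology samples are analyzed: days 0 and 90, month 8½". Section 10.4.2 adds "Titres of anti-HBs and anti-CS antibodies at the following time points for which serology samples are analyzed: month 21". The serology plan (5.8.4) and the label list in Appendix G agree, apart from 5.8.4 calling the month 8½ draw month 9.
- **Seroprotection (10.7.4).** The former decision sentence is struck out. Its replacement repeats the sample-size text of 10.6.2: "A non-inferiority approach will be used to calculate the power of the study for the comparison of seroprotection rates", and "This sample size will have 89% power at a 2.5% significance level using a one-sided equivalence test of proportions", with assumed rates of 0.95 in both groups and a margin of 0.10. A separate sentence tabulates seroprotection at day 90 without comparing the groups.
- **Use of the result (5.2.12).** "If non-inferiority of the seroprotective anti-HBs response induced by RTS,S/AS02A, as compared to that afforded by Engerix-B™, is demonstrated in the statistical comparison", no Engerix-B cross-over is planned for the malaria vaccine group; otherwise a testing and vaccination plan starts at study end.

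**The concern.** Three things in 10.7.4 do not fit together.

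First, the GMT comparison names a time with no data. Someone would have to choose between day 90 and month 8½ later, possibly with results in hand.

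Second, two comparisons of the same antibody response, in the same children and the same section, carry different one-sided error rates (5% and 2.5%), and no reason is given.

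Third, the section says non-inferiority will be assessed for seroprotection, but no sentence says when it has been met or at which visit. Section 5.2.12 needs exactly that verdict. Section 1.2.2.5 also ties the hepatitis B comparison to whether RTS,S/AS02A could replace the hepatitis B antigen in the EPI schedule.

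**Working it through.** **Time point.** The Cohort 2 visit table labels day 90 as month 3, so month 4 is not another name for it. The field visits nearest month 4 (days 118 and 132, section 5.6) take finger-prick blood for a film and genotyping only. Anti-HBs is not measured between day 90 and month 8½.

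**Inputs (10.6.2).** 124 evaluable per group, from 416 × 0.80 × 0.75 / 2 = 124.8; SD 0.591 on the log10 scale; GMT margin 0.5, or log10(2) = 0.301; seroprotection 0.95 in both groups, margin 0.10.

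**GMT power.** SE = 0.591 × √(2/124) = 0.0751, and 0.301 / 0.0751 = 4.01.

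- One-sided 5%: Φ(4.01 − 1.645) = 0.991, which reproduces the stated 99%.
- One-sided 2.5%: Φ(4.01 − 1.960) = 0.980.

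**Seroprotection power.** The Farrington-Manning method takes the null variance from rates constrained to differ by 0.10, here 0.870 and 0.970.

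- Null SE = √[(0.8703 × 0.1297 + 0.9703 × 0.0297)/124] = 0.0338.
- Alternative SE = √(2 × 0.95 × 0.05/124) = 0.0277.
- One-sided 2.5%: Φ[(0.10 − 1.960 × 0.0338)/0.0277] = Φ(1.22) = 0.889, which reproduces the stated 89%.
- One-sided 5%: Φ(1.60) = 0.946, which matches the superseded 95%.

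**Table 7.** The same formulas at its sample sizes give these powers (%):

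| n per group | Seroprotection: stated | at 5% | at 2.5% | GMT: stated | at 5% | at 2.5% |
|---|---|---|---|---|---|---|
| 124 (text) | 89 | 94.6 | 88.9 | 99 | 99.1 | 98.0 |
| 112 | 92 | 92.3 | 85.1 | 99 | 98.5 | 96.8 |
| 99 | 89 | 88.9 | 79.8 | 98 | 97.4 | 94.8 |
| 87 | 85 | 84.6 | 73.7 | 96 | 95.7 | 91.9 |

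Table 7's seroprotection column therefore still reflects one-sided 5%. It shows 92% with 112 per group, while the text gives 89% with 124, although only sample size is meant to vary. Its GMT column fits two one-sided tests at 10% each (98.9, 97.9, 96.2%) slightly better than one-sided 5%; neither is one-sided 2.5%.

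**The case against.** - **The consequence in 5.2.12 does not hang on the GMT rule.** A reader might infer that the end-of-study hepatitis B plan is being decided at a looser error rate on data that do not exist. Section 5.2.12 refers to the seroprotective response and does not mention GMTs, so the month 4 label and the 90% interval do not drive it. This objection stands.
- **Seroprotection is not left without any rule.** A reader might conclude that nothing remains. The current text still fixes a one-sided test of proportions, alpha 2.5%, margin 0.10, comparator and age group, and tabulates seroprotection at day 90. A test with a stated margin and level implies its own criterion. This largely stands: what is missing is the explicit criterion and the visit for the comparison.
- **The two levels need not agree.** Sections 10.6.2 and 10.7.4 are consistent with each other on the 90% interval, and no current sentence requires a common alpha. The Amendment 2 summary speaks of moving to a 95% interval in 10.7.4, but a difference between a change summary and the current text is not in itself an error. That is fair, but the operative text still runs paired comparisons at different levels without explanation.
- **Day 90 is the natural reading, and the Report and Analysis Plan can settle details.** Day 90 is the obvious candidate. That plan is not shown and may add a criterion. It cannot, however, follow a protocol time point at which no serum exists.

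**Conclusion.** The point holds as a defect of specification. The GMT comparison cannot be carried out at its stated time and uses twice the one-sided error rate of its companion. The seroprotection comparison, on which 5.2.12 depends, has an inferable margin and level but no written success criterion or visit.

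The numerical effect is small. Aligning the GMT level lowers power from 99.1% to 98.0% with 124 per group, and by at most about 4 points (95.7% to 91.9%) with 87 seronegative children per group. The larger gaps in Table 7's seroprotection column (92/89/85% shown, about 85/80/74% at 2.5%) are not a cost of the change, because the text already sets 2.5% for that comparison.

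These figures rest on the protocol's SD of 0.591, rates of 0.95 and a true GMT ratio of 1. The seroprotection figures also depend on the Farrington-Manning method, chosen because it reproduces the stated 89%; at 2.5% with 124 per group, an unpooled formula gives 95.1% and a continuity-corrected one 91.3%.

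The comparison is secondary and confined to Cohort 2. The primary malaria endpoint and the enrolment target are unaffected, so this is something that should be fixed rather than a bar to the trial.

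**What to change.** In section 10.7.4:

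- State that both comparisons use the day 90 sample (30 days after dose 3).
- Seroprotection: non-inferiority is shown if the lower limit of the two-sided 95% CI for the difference in rates, RTS,S/AS02A minus Engerix-B, exceeds -10%.
- GMT: non-inferiority is shown if the lower limit of the two-sided 95% CI for the ratio, RTS,S/AS02A over Engerix-B, exceeds 0.5.
- Delete the pasted power paragraph, which belongs in 10.6.2.
- Reconcile the day 90 tabulation, which still names children of 18 months or more, with the 24-month limit used for the comparison.

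In section 10.6.2:

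- Restate GMT power as 98% at one-sided 2.5% with 124 per group, in place of 99% at alpha 10%.
- Recompute Table 7 at one-sided 2.5%: about 85/80/74% for seroprotection and 97/95/92% for GMT with 112/99/87 per group.

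Section 5.2.12 already names the seroprotective response and needs no change for this purpose. The cost is protocol wording, settled before the blind is broken, plus the GMT power loss given above; no subjects, visits or samples are added.
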